### 8.1.3 Other study parameters (if applicable)

In order to report characteristics of the study population and to determine treatment costs, patient characteristics, additional injury-related and outcomes-related variables will be collected. These will include:

#### Patients characteristics to be collected:

- Age (calculated from date of birth and date of treatment)
- Gender (male or female)
- Medical history (diabetes, Raynaud's disease, rheumatoid arthritis, peripheral nerve injury, vascular diseases, or other (text))
- American Society of Anesthesiologists (ASA) classification (ASA 1, 2, 3, 4, 5, or unknown)
- Pre-injury occupation (work, hobby, sports) (text description) and hours spent per week (text))
- Hand dominance (left or right; for patients with upper extremity injuries only)
- Eye dominance (left, right, unknown; for patients with eye injuries only)

#### Additional injury characteristics to be collected:

- Injury occurred within the permitted period to set off fireworks (determined by the date and time of injury and the legally permitted period to set off fireworks)
- Type of fireworks (sparklers, firecrackers, roman candles, rockets, shells/mortars, carbid, homemade, other (text), or unknown)
- Role (igniter, bystander, other, or unknown)
- Legal fireworks (yes, no, or unknown)
- Correct use of fireworks (yes, no, or unknown)
- Setting of injury (domestic, work related, professional firework display, other (text), or unknown)

#### Treatment characteristics to be collected:

- Prehospital transport (ambulance, Helicopter Emergency Medical Services (HEMS), self-transport, other (text), or unknown)

- HEMS assistance (yes, no, or unknown)
- Referral to hospital (direct or indirect (general practitioner, general practice center, other hospital, or other (text)))
- Admission (yes or no)
- Required care (ward, Intensive Care Unit (ICU), observatory, or other)
- Wound treatment (wound dressings (text), topical therapy (text), other (text), unknown, or not needed)
- Number of transfusions required (packed-cells, platelets, plasma, colloid, or other (text description))
- Discharge destination (home, other hospital, nursing home, rehabilitation facility, burn center, or other)
- Need for prosthesis (yes or no, and description)

Outcome-related variables to be collected:

- Time between initial injury and hospital presentation (calculated from dates of trauma and hospital presentation)
- Duration of hospital admission (calculated from date of admission and date of discharge)
- Duration of ICU admission (in days) (calculated from dates of admission and discharge)
- Mortality (fireworks-related, yes or no)
- Rehabilitation (physical therapy, hand therapy, ergotherapy, other (text description), or multiple)
- Complications and secondary interventions (text description)

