The fireworks-related injuries in the Netherlands are concentrated around the night of New Years' Eve. Every year the fireworks-related injuries are recorded by the Dutch Society of Ophthalmology, Dutch Association of Plastic Surgeons and the Dutch Trauma Society. Since 2004, also a nationwide estimation on the number of fireworks-related injuries is made by the Consumer Safety Institute (2, 8). However, this number is an estimation based on a sample of Dutch hospitals. Detailed information about patient and injury characteristics, medical and societal costs and long-term functional outcomes are lacking. This kind of information aids the public debate and contributes to the political decision on whether or not to abolish the use of consumer fireworks.

Fireworks-related injuries are relatively easy to prevent and therefore a relevant public health problem. However, detailed knowledge is lacking on the treatment, functional impairment, and medical and societal costs on the long-term. This study aims to provide detailed information regarding patient, injury, and treatment characteristics, medical and societal costs, and patient-reported outcomes, with a follow-up of one year.

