## 4. STUDY POPULATION

### 4.1 Population (base)

All patients (no age limit) with fireworks-related injuries presenting to a hospital in the period between December 1, 2017 and January 31, 2018 in the Trauma Region Southwest Netherlands, will be eligible for inclusion. Patients will be recruited from every hospital in the Trauma Region Southwest Netherlands. In the Netherlands it is only permitted to lit fireworks as a consumer during the celebration of New Year's Eve and logically most fireworks-related injuries occur during that night or the period close before and after. Therefore, this specific time range was chosen.

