### 10.1 Primary study parameter(s)

Injury characteristics will be analyzed descriptively. They will be reported as mean with Standard Deviation (SD; parametric, continuous data) or median with quartiles ( $P_{25}$ - $P_{75}$ ; non-parametric, continuous data), or as number with percentage (categorical data).

Data will be reported as a group as well separately for the groups of patients with eye injury, upper and lower extremity injury, hand injury, or burn wounds. Further subgroups will be determined based on the patients included. Relevant subgroups can be legal versus illegal fireworks, operator versus bystander.

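### Delay from injury to hospital is derived from calendar dates with no unit, so any delay under 24 hours is reduced to whether midnight was crossed

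*Protocol*

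**What the plan says.** Among the outcome-related variables in protocol section 8.1.3 is "Time between initial injury and hospital presentation (calculated from dates of trauma and hospital presentation"). No clock time enters the calculation and no unit is given. A few lines further on, the intensive care item does carry a unit: "Duration of ICU admission (in days) (calculated from dates of admission and discharge").

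The same section uses clock time where it is wanted. Whether an injury fell inside the legal period is "determined by the date and time of injury and the legally permitted period to set off fireworks". Time of injury is therefore to be obtained, but no time of hospital presentation is listed.

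On timing, section 1 states: "The fireworks-related injuries in the Netherlands are concentrated around the night of New Years' Eve". Section 4.1 adds that "logically most fireworks-related injuries occur during that night or the period close before and after".

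On reporting, section 10.3 sends the other parameters to 10.2, which follows 10.1. Continuous data there are summarised thus: "They will be reported as mean with Standard Deviation (SD; parametric, continuous data) or median with quartiles". Section 10 rules out imputation of missing values.

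**The concern.** Subtracting one date from another gives whole days. For a patient who reaches hospital within hours, the result does not measure how long that took. It records only whether the date changed on the way. In a cohort spread over all hours of the day this would be a modest blur. Here the injuries are expected on the one night when the change of date lies in the middle of the busy period, so many short delays may straddle it.

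At stake is the description of time to presentation. Two patients can be placed in reverse order, and a mean or median of such values says little about same-night presenters. Groups whose injuries occur at different hours could also appear to differ in delay when they do not.

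This is not a detail that a protocol would normally leave to the analysis plan. The protocol itself fixes the derivation, and a presentation time that is not collected cannot be supplied by an analysis plan.

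**Working it through.** The protocol gives no figure for delay, so there is none to reproduce. The check applies the stated rule.

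**Inputs from the protocol.** The rule uses dates only (8.1.3). Injuries concentrate on New Year's Eve night (sections 1 and 4.1).

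**Inputs assumed.** The clock-time distribution of injuries and the distribution of delay are not given.

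**Formula.** Let t be the time of injury in hours from midnight and d the true delay in hours. Then

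recorded days = floor((t + d)/24) − floor(t/24).

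**Step 1, no assumptions needed.** For d below 24, the result is 0 or 1, and it is 1 only if midnight lies between injury and presentation. In reverse:
- a recorded 0 covers true delays from 0 to just under 24 hours;
- a recorded 1 covers a few minutes to just under 48 hours;
- a recorded 2 or more means more than 24 hours.

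**Step 2, worked examples.**

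| Injury | Presentation | True delay | Recorded |
|---|---|---|---|
| 23:50 | 00:30 next day | 40 minutes | 1 day |
| 00:30 | 23:00 same day | 22.5 hours | 0 days |

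The order is reversed.

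**Step 3, simple illustration.** Assume injuries spread evenly over the 8 hours from 20:00 to 04:00 and the same delay D for everyone, with D at most 4 hours. The share recorded as 1 day is D/8:
- D = 1 hour: 1/8 = 12.5%
- D = 2 hours: 2/8 = 25%
- D = 3 hours: 3/8 = 37.5%

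The rest are recorded as 0, although all patients have the same delay.

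**Step 4, sensitivity to the assumptions.** A simulation (400,000 draws per scenario) used lognormal delays with log-SD 1. Injury times were clustered on the night in three ways: normal around 00:30 with SD 2 hours, uniform 18:00-06:00, and uniform 18:00-02:00.
- With a median delay of 1 to 4 hours, 96% to 99.9% of delays were under 24 hours. Of those, 13% to 47% were recorded as 1 day, and the correlation between recorded and true delay was 0.15 to 0.43.
- With injuries normal around 00:30 and a median delay of 2 hours, 27% of the delays under 24 hours were recorded as 1 day. Their median true delay was 2.9 hours, against 1.7 hours among those recorded as 0.
- With a median delay of 12 hours, about 75% of delays were under 24 hours, and 14% to 18% of all patients had a recorded value of 2 days or more. The variable then does separate some late presenters.

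**Step 5, a possible false group difference.** Suppose one group's injuries fall evenly over 20:00-04:00 and another's over the whole day, and all delays are 2 hours. Then 2/8 = 25% of the first group and 2/24 = 8.3% of the second are recorded as 1 day. Section 10.1 names legal versus illegal fireworks as a possible subgroup, but the protocol does not say how injury times differ between the two.

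**The case against.** Four points deserve weight.

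1. *The wording may be shorthand.* No unit is stated, injury time is to be obtained anyway, and the case report form is not available to us. The variable might in practice be built from time stamps. That cannot be excluded. However, the same section writes date and time where it means both, and lists no presentation time, so the literal reading is the better supported one.

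2. *The variable keeps information on late presenters.* This stands. Delays beyond a day are plausible, since the protocol allows for "Referral to hospital (direct or indirect (general practitioner, general practice center, other hospital, or other (text"))), and a value of 2 or more reliably means over 24 hours. A reader might infer that the item says nothing about delay at all; the arithmetic does not support that.

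3. *The size is assumed.* This also stands. The protocol speaks of the night, not of midnight, and gives no delay distribution. A reader might infer that most of the cohort cannot be told apart, or that every description of delay would be an artefact of the clock. Both depend on most delays being well under a day, which is reasonable but not documented.

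4. *The item is minor.* It is not the primary outcome, a secondary objective or a secondary endpoint, and no planned test uses it. The only tests specified, in section 10.3, compare participants with non-participants on gender, injury location and age. A reader might see it as a key time-to-care measure, but the protocol gives it no such role.

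**Conclusion.** The point holds in limited form. As written, the rule in 8.1.3 turns every delay under 24 hours into a marker of a midnight crossing and can reverse the order of same-night presenters. That follows from the rule alone and needs only the literal reading of dates. How many patients are affected is unknown. The 12.5% to 37.5% in the simple illustration, and the 13% to 47% of delays under 24 hours in the simulations with a median delay of 1 to 4 hours, rest entirely on assumed injury times and delays. Late presenters, with a difference of 2 days or more, are still identified. Severity is low: the likely harm is one uninformative or misleading descriptive result, and no study objective is affected.

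**What to change.** In section 8.1.3, define the delay in hours, calculated from date and time of injury and date and time of hospital presentation. Injury time is already needed for the legal-period variable. Presentation time is one added field, to be taken from the hospital file that section 8.3 already has extracted.

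Where a clock time is missing at either end, keep the date difference as a coarse category: 0 or 1 day as not resolvable, 2 days or more as over 24 hours. Setting all such cases to unknown would be worse. Clock times may be poorest for patients who come late, and with no imputation their long delays would drop out selectively, making presentation look prompter than it was.

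The cost is a wording change and one field. Some injury times will be approximate, and the protocol does not say how completely hospital files record the time of presentation.

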## **8.2 Randomization, blinding and treatment allocation**

Randomization and treatment allocation are not applicable, since this study is not an intervention study. Blinding of patients and surgeons also does not apply.

## **8.3 Study procedures**

### A: Patient selection

The local contact person in the participating hospital will provide details of each patient with fireworks-related injuries to the research team. A simple e-mail or phone call is sufficient for registration, the coordinating investigator (or a dedicated and trained research assistant) will take care of all further logistics and data collection. He/she will also call each hospital on a daily basis during the inclusion period in order to ask for any

missed registrations. As a check for completeness of inclusion, hospital registries will be searched by the coordinating investigator or research assistant.

#### B: Data collection

Patients will be followed for one year, with the first visit for baseline measurement planned as soon as possible, preferably within two weeks. Follow-up visits are planned at three months (window 2-4 months), six months (5-7 months), and 12 months (window 12-14 months) after presentation.. In case of early discharge from clinical treatment/follow-up, subsequent follow-up can be performed by visiting patients at home.

The study will not interfere with treatment or follow-up. Data concerning patient characteristics, injury characteristics, treatment details, and clinical outcome data will be extracted from the patient file as much as possible. These data will be collected from the patient's medical files as soon as possible after signing informed consent. For the purpose of the study, additional details concerning treatment and outcome (see paragraph 8) that are not mentioned in the patient's hospital files, will be registered on the case report forms directly. This will be done at the follow-up visits.

As soon as possible and within two weeks after inclusion patients will be asked to complete the questionnaire's, reflecting their pre-injury health status. For all participants this will be the EQ-5D-3L questionnaire. For patients with eye trauma the HUI-3 (domain vision), for patients with upper extremity trauma the HUI-3 (domain dexterity), the *Quick-DASH*, and CISS, for patients with lower extremity trauma the LEFS, and for patients with burn wounds the POSAS. At three, six and 12 months, treatment characteristics, health care consumption details and patient reported outcomes will be collected.

**Table 1: Follow-up schedule and data collection**

| Event forms               | Screening | <2 weeks
(<2 we) | 3 months
(2-4 mo) | 6 months
(5-7 mo) | 12 months
(12-14 mo) |
|---------------------------|-----------|---------------------|----------------------|----------------------|-------------------------|
| Screening                 | X         |                     |                      |                      |                         |
| Informed Consent          |           | X                   |                      |                      |                         |
| Patient characteristics   |           | X                   |                      |                      |                         |
| Injury characteristics    |           | X                   | X                    |                      |                         |
| Radiology                 |           | X     | X        | X        | X           |
| Digital photo             |           | X     | X        | X        | X           |
| Treatment characteristics |           | X                   | X                    | X                    | X                       |
| Outcome details           |           | X                   | X                    | X                    | X                       |
| Adverse events            |           | X                   | X                    | X                    | X                       |
| Health care consumption   |           | X       | X                    | X                    | X                       |

|                                                    |                |   |   |   |
|----------------------------------------------------|----------------|---|---|---|
| Work or school absence                             | X  | X | X | X |
| EQ-5D-3L                                           | X  | X | X | X |
| HUI-3 domain vision                    | X  | X | X | X |
| HUI-3 domain dexterity                 | X  | X | X | X |
| Quick-DASH                             | X  | X | X | X |
| CISS                                   | X  | X | X | X |
| LEFS                                   | X  | X | X | X |
| POSAS                                  |                | X | X | X |
| Satisfaction with functional recovery and cosmesis |                | X | X | X |
| View on fireworks                                  |                |   | X |   |
| Early withdrawal                                   | *              | * | * | * |

 Only if treating physician requests radiographs;  Representing the pre-injury status,  Optional;

 For patients with eye injury,  For patients with upper extremity injury,  For patients with lower extremity injury,  For patients with burn wounds. \* Only at time of withdrawal

For EQ-5D and HUI-3, pediatric versions are available for children <16 years. Parents of children <16 years complete the POSAS. Other questionnaires are completed by patients ≥16 years only.

#### 8.4 Withdrawal of individual subjects

Participants can leave the study at any time for any reason if they wish to do so without having to give a reason. Their decision to withdraw will have no consequence for their medical treatment. The investigator can decide to withdraw a subject from the study for urgent medical reasons.

##### 8.4.1 Specific criteria for withdrawal (if applicable)

Not applicable

#### 8.5 Replacement of individual subjects after withdrawal

Not applicable; no replacement will take place.

#### 8.6 Follow-up of subjects withdrawn from treatment

Should a participant who is still under routine clinical follow-up decide to withdraw consent, they will receive the normal clinical follow-up as any other patient treated for fireworks-related injuries. As treatment are not part of this study, no additional controls are needed. Also, the research team will no longer contact patients after consent has been withdrawn.

#### 8.7 Premature termination of the study

This will not occur, as treatment is not part of the study.

## **9. SAFETY REPORTING**

As this study is not subject to the Medical Research Involving Human Subjects Act (WMO), patients are not subjected to treatment in this study, and the study does not involve an investigational or non-investigational medicinal product, this paragraph does not apply.

### **9.1 Temporary halt for reasons of subject safety**

As patients are not subjected to treatment in this study, this does not apply.

### **9.2 AEs, SAEs and SUSARs**

#### **9.2.1 Adverse events (AEs)**

As patients are not subjected to treatment in this study, this does not apply.

#### **9.2.2 Serious adverse events (SAEs)**

As patients are not subjected to treatment in this study, this does not apply.

#### **9.2.3 Suspected unexpected serious adverse reactions (SUSARs)**

As patients are not subjected to treatment in this study and the study does not involve an investigational medicinal product, this does not apply.

### **9.3 Annual safety report**

As patients are not subjected to treatment in this study and the study does not involve an investigational medicinal product, this does not apply.

### **9.4 Follow-up of adverse events**

As patients are not subjected to treatment in this study, this does not apply.

### **9.5 Data Safety Monitoring Board (DSMB) / Safety Committee**

As patients are not subjected to treatment in this study and the study does not involve an investigational nor a non-investigational medicinal product, participants will have no larger risks than patients who are not participating in this study. Therefore, no DSMB will be installed.

## 10. STATISTICAL ANALYSIS

Data will be analyzed using the Statistical Package for the Social Sciences (SPSS) version 21.0 or higher (SPSS, Chicago, Ill., USA). Normality of continuous data will be tested with the Shapiro-Wilk test, and homogeneity of variances will be tested using the Levene's test. A p-value <0.05 will be taken as threshold of statistical significance in all statistical tests, and all tests will be two-sided. Missing values will not be replaced by imputation.

### 10.1 Primary study parameter(s)

Injury characteristics will be analyzed descriptively. They will be reported as mean with Standard Deviation (SD; parametric, continuous data) or median with quartiles ( $P_{25}$ - $P_{75}$ ; non-parametric, continuous data), or as number with percentage (categorical data).

Data will be reported as a group as well separately for the groups of patients with eye injury, upper and lower extremity injury, hand injury, or burn wounds. Further subgroups will be determined based on the patients included. Relevant subgroups can be legal versus illegal fireworks, operator versus bystander.

### 10.2 Secondary study parameter(s)

Secondary outcome measures will be analyzed and reported the same as described for the primary outcome measures (paragraph 10.1). The only difference is that costs will be reported as mean with 95% confidence interval (95% CI). The 95% CI around the mean costs will be approximated by nonparametric bootstrapping.

### 10.3 Other study parameters

See section 10.2.

In order to check if the enrolled sample is a true representation of the total group of patients treated in a hospital for fireworks-related injuries. Gender and location of injuries of participants and non-participants will be compared using a Chi-squared test or Fisher's test. Differences in age between the two groups will be tested using a Student's T-test or Mann-Whitney U-test, as applicable.

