### 4.4 Sample size calculation

A report from VeiligheidNL mentions 574 patients during the annual change of year in 2014-2015 in The Netherlands. With 2 full months for inclusion we expect to increase this by at least 10% ( $n=638$ ). The Southwest Netherlands area contains 10 of the 90 Dutch hospitals. This could project to a possible sample of 70-80 patients. A formal sample size calculation for this observational study is not constructive. By including all patients treated in the Trauma Region Southwest Netherlands during the specific time interval, the largest possible sample will be enrolled. The larger the number of patients, the more reliable the analysis will be. Enrolling all patients possible will result in the highest reliability of data (*i.e.*, accurate point estimate with lowest possible variance).

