## 8. METHODS

### 8.1 Study parameters/endpoints

#### 8.1.1 Main study parameter/endpoint

The primary outcome measures are the **injury characteristics**. The following variables will be collected:

- Number of injuries
- Body site injured
  - 1) Head/neck (scalp, forehead, orbital, nose, cheek, mouth/lips, chin, ear, or neck)
  - 2) Eye
  - 3) Upper extremity (shoulder, upper arm, elbow, lower arm, wrist, hand palm, hand dorsum, thumb/first webspace, digit 2, 3, 4, 5, or other (text))
  - 4) Lower extremity (hip, upper leg, knee, lower leg, ankle, foot, other (text))
  - 5) Trunk (chest, abdomen, back, pelvis, or other (text))
  - 6) Other (text)
- Injured side (left, right, or not applicable)
- Type of injury per site (including text description)
  - 1) Burn (total body surface area (TBSA) and degree)
  - 2) Globe rupture (open or closed)
  - 3) Intra-ocular foreign body
  - 4) Penetration/perforation
  - 5) Corneal/adnex burn (chemical or thermic)
  - 6) Lens injury
  - 7) Retina injury
  - 8) Choroidal injury
  - 9) Corneal rupture
  - 10) Soft tissue damage (superficial or deep)
  - 11) Fracture/dislocation (fracture location)
  - 12) Amputation (level of amputation))
  - 13) Vascular damage (affected vessel)
  - 14) Neurological damage (affected nerve)
  - 15) Tendon damage (affected tendon)
  - 16) Other (text)

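### Representativeness is checked only by low-powered significance tests on gender, injury location and age, so a non-significant result cannot show it, and injury severity is not compared

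*Protocol*

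**What the plan says.** Protocol section 10.3 gives the purpose of the comparison as "In order to check if the enrolled sample is a true representation of the total group of patients" treated in a hospital for these injuries. It names three variables. For the categorical ones, "Gender and location of injuries of participants and non-participants will be compared using a Chi-squared test or Fisher's test". For age, "Differences in age between the two groups will be tested using a Student's T-test or Mann-Whitney U-test, as applicable". Section 10 supplies the criterion: "A p-value <0.05 will be taken as threshold of statistical significance in all statistical tests, and all tests will be two-sided".

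Section 10.3 states no tolerated difference and no interval estimate, and does not say what follows if a difference is found. It does not say how location is coded. Section 8.1.1 begins the primary outcome with "Number of injuries" and then records body site and type of injury per site, so one patient can contribute several sites.

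On size, section 4.4 projects 70-80 patients in the region and gives no participation rate.

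**The concern.** The question in 10.3 is whether two groups are alike. A significance test answers a different question: whether the data are hard to reconcile with no difference. With a few dozen patients, the test will often be non-significant when the groups differ by an amount that matters. The stated purpose and the single p<0.05 threshold leave the p-value as the only criterion on the page.

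The choice of variables adds to this. The primary outcome includes burn extent and degree, amputation level, fractures, and vascular, nerve and tendon damage. If willingness to take part depends on how badly someone was hurt, the primary percentages are distorted directly. Gender, age and location need not reveal it. Section 1 intends the results to inform public debate and a political decision, so a claim of representativeness would carry weight.

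**Working it through.** **Projected size.** Section 4.4 starts from "A report from VeiligheidNL mentions 574 patients during the annual change of year in 2014-2015 in The Netherlands", adds 10 per cent for the two-month window to give 638, and takes a regional share ("The Southwest Netherlands area contains 10 of the 90 Dutch hospitals").
- 574/0.9 = 637.8, which rounds to the stated 638 (574 × 1.1 would be 631.4).
- 637.8 × 10/90 = 70.9, and 631.4 × 10/90 = 70.2. Both fall in the stated 70-80. The upper end of 80 is not derived.

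**Inputs.** Two-sided alpha 0.05 (section 10). Male proportion 76% (section 1). Total about 75 (section 4.4). *Assumed:* 50 participants and 25 non-participants, with 35 versus 35 and participation of 50-90% as checks. *Assumed differences:* 10 and 20 percentage points for gender, 0.3 SD for age.

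**Gender.** Exact power is the sum of the two binomial probabilities over all tables with p<0.05.

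| Split | Male % | Fisher | Chi-squared |
|---|---|---|---|
| 50 vs 25 | 76 vs 66 | 0.11 | 0.16 |
| 50 vs 25 | 76 vs 56 | 0.35 | 0.44 |
| 35 vs 35 | 76 vs 66 | 0.10 | 0.15 |
| 35 vs 35 | 76 vs 56 | 0.34 | 0.43 |

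Hand check for 50 versus 25 and 76% versus 66%: the pooled proportion is (38 + 16.5)/75 = 0.727. The null SE is √(0.727 × 0.273 × (1/50 + 1/25)) = 0.109. The alternative SE is √(0.76 × 0.24/50 + 0.66 × 0.34/25) = 0.112. Power ≈ Φ((0.10 − 1.96 × 0.109)/0.112) = Φ(−1.01) ≈ 0.16.

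**Age.** The noncentrality is 0.3 × √(50 × 25/75) = 1.22 on 73 degrees of freedom, giving power 0.23. For 35 versus 35 it is 0.24.

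**Sensitivity to the split.** For totals of 70-80 and participation of 50-90%, power is 10-17% for 10 points, 23-47% for 20 points and 11-27% for 0.3 SD. A gender difference detectable with 80% power is about 31-51 points. Detecting 10 points with 80% power needs 323 per group. If the 70-80 were all participants and non-participants came on top, power for a 15-point gender difference would be about 35% (75 versus 30) to 51% (75 versus 75).

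**Severity-only selection.** If the groups differ in severity but not in gender, location or age, and the three tests are treated as independent, all three are non-significant with probability 0.95³ = 0.857.

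**What an interval would show.** The 95% half-width for the gender difference is 1.96 × √(0.76 × 0.24 × (1/n₁ + 1/n₂)):
- 0.187 for 40 versus 40
- 0.205 for 50 versus 25
- 0.234 for 64 versus 16

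**Why no fixed standardised-difference cutoff.** At 50 versus 25 the SE of a standardised difference is about √(1/50 + 1/25) = 0.245. With no true difference, |SMD| exceeds 0.1 with probability 2(1 − Φ(0.41)) ≈ 0.68 and exceeds 0.2 with probability 2(1 − Φ(0.82)) ≈ 0.41, for each variable.

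**The case against.** Four points are fair.

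*The protocol nowhere writes that p>0.05 means representative.* True. That reading is implied by the stated purpose and the threshold. It stands as an implication only, and one sentence in 10.3 would remove it.

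*A reader might infer that body sites are treated as mutually exclusive and that the location test is therefore invalid.* The text does not support this. Coding is not given, a yes/no test per site fits the wording equally well, and section 10.1 already reports overlapping injury groups. A single pooled table with patients in several cells would be invalid, but the protocol does not prescribe one.

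*A reader might infer that this is the only protection against participation bias and that it would nearly always pass.* Neither holds. Section 8.3 provides daily calls to hospitals and a registry search. Section 11.2 offers consent for use of medical files alone to patients put off by the questionnaires, which protects the primary outcome. If gender, a body site and age all differ at once, at least one test is significant in about 46-64% of cases (15 points, 15 points, 0.3 SD) or 70-90% (20 points, 20 points, 0.5 SD), with participation of 50-80%, an assumed site prevalence of 40% and independent tests.

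*A missed difference is not the bias.* Bias in the sample is (1 − participation) times the difference. At 50 of 75, a 10-point difference shifts the estimate by 3.3 points and a 20-point difference by 6.7, against a sampling half-width of 1.96 × √(0.76 × 0.24/50) = 11.8 points. This limits the harm. It also favours reporting the size of the difference, from which the shift can be read, over reporting a p-value.

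**Conclusion.** The point holds in limited form. At the projected size, the tests in 10.3 cannot support a conclusion that the sample is representative, and they do not examine severity. Power is about 11-16% and 35-44% for gender differences of 10 and 20 points, and about 23% for 0.3 SD in age. These figures rest on an assumed 50 to 25 split and assumed differences. Other splits of 70-80 patients leave the conclusion unchanged. Consent for medical files alone would probably shrink the non-participant group and lower power further.

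It does not follow that the sample will be biased, that any bias would be large, or that the descriptive primary analysis is wrong. The comparison is an ancillary check, and the weakness lies in what can be concluded from it.

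**What to change.** In section 10.3:
- Replace the tests by participant versus non-participant differences with 95% confidence intervals for age, sex and each body site. Code each site as one yes/no indicator per patient, since a patient may have several.
- Add admission (yes/no) as a severity marker where it may be obtained for non-participants.
- State that representativeness will be judged from the size and interval of these differences and not from p>0.05, with no fixed standardised-difference cutoff.

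Weighting the results to all treated patients is at most an optional sensitivity analysis. Weights built on age, sex and site would still leave severity out.

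The cost is a rewording of 10.3 and one table. Age, gender and location of non-participants are already planned. Admission status is a new item for them and depends on permitted access. The intervals will be wide, about 19-23 points either side for gender, so the report will be able to claim less about representativeness.
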